
### EEG power spectrum processing

2.5

Frontal quantitative EEG parameters will be obtained using the ConView YY-105 anesthesia depth monitoring system, employing bilateral frontal electrodes at a sampling rate of 500 Hz. EEG power spectral density will be estimated using the multitaper method (15 tapers, time-half bandwidth product = 8) with a 4-s window length and 50% overlap (2-s step), implemented in MATLAB’s pmtm function. The bandpass filter (0.5–45 Hz) will be applied as a zero-phase filter using forward-reverse filtering to avoid phase distortion. Artifact-free epochs will be extracted at six predetermined time points: T0 (pre-stimulation baseline): 5 min prior to the first taVNS session; T1 (preoperative sustained stimulation), 20–30 min following the initiation of taVNS; T2 (post-induction), 5 min after tracheal intubation; T3 (intraoperative maintenance), 20 min subsequent to the skin incision; T4 (peri-extubation), at the conclusion of surgery, immediately preceding emergence from anesthesia; and T5 (postoperative sustained stimulation), 20–30 min after the initiation of postoperative taVNS.

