### Sample size calculation

2.10

The primary outcome is the incidence of POSD on POD 1, defined as an AIS score ≥ 6. Based on our internal pilot study (*N* = 20; taVNS *n* = 10, sham *n* = 10), the incidence of POSD (AIS ≥ 6) was 20% in the taVNS group compared to 45% in the sham group. Sample size was calculated using PASS 15.0 (NCSS, LLC) for a two-sided chi-square test comparing two independent proportions, with the following parameters: P1 (sham) = 0.45, P2 (taVNS) = 0.20, α = 0.05 (two-sided), power = 0.80. This calculation indicated a need for 52 evaluable participants per group. Accounting for an anticipated 10% dropout rate based on comparable perioperative neuromodulation trials, the final target enrollment is 116 participants (58 per group).

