### Statistical analysis

2.11

Statistical analyses will be performed using SPSS Statistics 26.0 (IBM Corp.) and R 4.4.0 (R Foundation). MATLAB R2018b (MathWorks, Natick, MA) will be employed for the preprocessing and spectral analysis of EEG data. Normality will be assessed using the Shapiro-Wilk test and Q-Q plots. Continuous variables will be presented as mean ± standard deviation or median (interquartile range), and categorical variables will be shown as frequencies and percentages.

The primary outcome (incidence of AIS ≥ 6 on POD 1) will be analyzed using the chi-square test to compare proportions between the taVNS and sham groups. The effect size will be expressed as an absolute risk reduction with a 95% confidence interval. Linear mixed-effects models will analyze repeated measures, including (1) AIS total scores (Pre 1 to POD 3); (2) HADS-A and HADS-D (as two separate scales, Pre 1 to POD 3); (3) objective sleep parameters from actigraphy; and (4) EEG spectral power across five bands (delta, theta, alpha, beta, and gamma) at six time points (T0–T5). Models include fixed effects for group, time, group × time interaction, and random intercepts for subjects. For repeated clinical outcomes, Bonferroni correction will be applied across four key endpoints: HADS-A, HADS-D, AIS trajectory, and objective sleep parameters from actigraphy, yielding a significance threshold of α = 0.0125 (0.05/4). For EEG spectral analyses, given the exploratory nature and high dimensionality (5 frequency bands × 6 timepoints), the Benjamini–Hochberg procedure will control the false discovery rate at q < 0.05.

A three-step approach will be used to identify predictors of POSD: (1) Univariate screening (*P* < 0.10) for 30 EEG variables (5 bands × 6 timepoints); (2) LASSO regularization (10-fold CV) to select independent predictors; (3) Multivariable logistic regression reporting ORs and 95% CIs.

The main analysis will adhere to the intention-to-treat methodology. To address missing data, multiple imputation via chained equations will be utilized, generating 20 imputations under the assumption that data are missing at random. Sensitivity analyses will incorporate pattern-mixture models to account for mechanisms where data are missing not at random. The per-protocol analysis will exclude cases with significant protocol deviations. Effect sizes will be reported as Cohen’s d, alongside 95% confidence intervals.

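### The 95% intervals for EEG predictors of POSD are ordinary ones reported after outcome-driven selection, so they will not cover at 95%; calling the predictors independent also needs arm in the model

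*Protocol article*

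**What the plan says.** Section 2.11 of the protocol article sets out three steps for identifying predictors of POSD. Step 1 is "Univariate screening (*P* < 0.10) for 30 EEG variables (5 bands × 6 timepoints"). Steps 2 and 3 follow: "2) LASSO regularization (10-fold CV) to select independent predictors; (3) Multivariable logistic regression reporting ORs and 95% CIs".

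The section mentions no sample split, no validation or resampling of the three steps together, and no interval that allows for selection. The 10-fold cross-validation belongs to step 2.

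The only candidates listed are EEG variables. For the mixed models, the same section does name the arm: "Models include fixed effects for group, time, group × time interaction, and random intercepts for subjects". For the predictor analysis it does not mention the arm at all.

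The Benjamini-Hochberg procedure is stated for the EEG spectral analyses. It is not tied to the predictor analysis, whose screen uses an uncorrected P < 0.10.

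Section 2.5 places T1 within the first stimulation session, and T5 at "20–30 min after the initiation of postoperative taVNS".

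**The concern.** A variable reaches step 3 only if it looked associated with POSD in step 1 and again in step 2. The logistic regression then estimates that association as if the variable had been named in advance. If the same patients are used throughout, the estimate is pushed away from the null and its ordinary interval ignores the selection. Cross-validation inside LASSO chooses the penalty. It does not validate the refit or widen its intervals.

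A second, separate issue concerns the description of the selected variables as independent. Five of the six timepoints (T1 to T5) fall after the first stimulation has begun. The protocol expects taVNS to change both the EEG and the POSD rate. If arm is not in the model, an EEG variable that taVNS shifts will correlate with POSD even when it has no link to sleep beyond arm.

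What is at stake is the biomarker reading of the trial. The Discussion says that even a null trial would inform biomarker reliability. Spurious predictors with confident-looking intervals would work against that aim.

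**Working it through.** **Inputs from the protocol article.** Section 2.10 gives "P1 (sham) = 0.45, P2 (taVNS) = 0.20, α = 0.05 (two-sided), power = 0.80", 52 evaluable and 58 enrolled per group, and 10% dropout. Section 2.11 gives 30 candidates (5 bands at 6 timepoints).

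**The plan's own sample size.** With unpooled variance, n = (1.960 + 0.842)² × (0.45 × 0.55 + 0.20 × 0.80) / 0.25² = 7.85 × 0.4075 / 0.0625 = 51.2, so 52 per group. Then 52 / 0.90 = 57.8, so 58 per group and 116 in total. The plan's figures are reproduced. (Pooled variance gives 54, which does not matter here.) No size is stated for the predictor analysis.

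**Events available.** The average planned rate is (0.45 + 0.20) / 2 = 0.325.
- 104 evaluable: 0.325 × 104 = 33.8 events, and 33.8 / 30 = 1.13 per candidate.
- 116 enrolled: 0.325 × 116 = 37.7 events, and 37.7 / 30 = 1.26 per candidate.

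**The screen alone.** If all 30 variables were unrelated to POSD, 30 × 0.10 = 3 would pass on average. If they were also independent of each other, at least one would pass with probability 1 − 0.90³⁰ = 0.958.

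**All three steps, with no EEG-POSD link.** Simulation with 104 patients, POSD rates of 45% and 20%, 300 trials per row, and no arm in the model. The documents do not give the correlation between timepoints (ρ, first-order autoregressive within band) or the penalty rule, so both are varied. The two rules are the penalty with the smallest cross-validated deviance (min) and the largest penalty within one standard error of it (1se).

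| Rule | ρ | Any variable selected | Any interval excluding 1 | Coverage of OR = 1 among selected | Median spurious OR per SD |
|---|---|---|---|---|---|
| min | 0 | 92% | 70% | 52% | 1.60 |
| min | 0.5 | 90% | 54% | 71% | 1.51 |
| min | 0.8 | 74% | 38% | 77% | 1.46 |
| 1se | 0 | 28% | 27% | 30% | 1.73 |
| 1se | 0.5 | 16% | 16% | 42% | 1.71 |
| 1se | 0.8 | 8% | 8% | 32% | 1.73 |

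The median OR ignores direction. With 300 trials, the standard error of a trial-level percentage is at most √(0.25 / 300) = 2.9 points. The last row's coverage rests on only 25 trials with any selection.

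A separately programmed simulation (116 patients, 330 trials, correlation 0.5 across times and 0.3 across bands, penalty rule not recorded) gave 85% of trials selecting a variable, 37% with one at p < 0.05, and coverage of about 80%.

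**Does arm repair the intervals?** With ρ = 0.5, the min rule and no arm effect on EEG, coverage was 71% without arm and 72% with arm in the final model. It does not.

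**Does arm matter for independence?** T1 to T5 contribute 5 × 5 = 25 of the 30 variables. Assume that taVNS shifts delta and alpha at T1 and T5, and that these variables have no effect on POSD given arm (ρ = 0.5, min rule). The table shows how often at least one of the four is declared significant.

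| Assumed shift | Arm not in final model | Arm in final model |
|---|---|---|
| none | 11% | 9% |
| 0.5 SD | 23% | 11% |
| 0.8 SD | 33% | 11% |

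Adding arm brings the rate back close to the no-shift level. The remainder is the selection fault itself.

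**The case against.** The strongest reply is that this is exploratory work. The Introduction speaks only of exploring EEG biomarkers, section 2.11 calls the EEG spectral analyses exploratory, and the predictor model is not a listed outcome. No treatment conclusion rests on it. That stands and limits the severity. It does not make a 95% interval correct when its coverage is far lower.

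A second reply is that LASSO is meant for many candidates and few events. That is fair: the low number of events per candidate is not a separate fault. It shows how unstable the selection will be. The fault is the ordinary interval reported after selection.

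A third reply is that the full analysis plan may add a split, a bootstrap or the arm. The article states none of these, and its silence should not be read as ruling them out. About 34 to 38 events leave little room for a split. Adding arm alone would leave the interval problem in place.

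A reader might also infer four stronger points that the material does not support:
- **That leaving out arm is what invalidates the intervals.** Coverage was almost the same with and without it.
- **That step 3 excludes arm.** The article lists the candidates for screening, not every covariate of the final model.
- **That the trial will usually report a significant predictor when none exists.** In most scenarios something is usually selected, but a significant result ranged from 8% to 70%, and the penalty rule drives much of that range.
- **That any EEG variable moved by taVNS is a false marker.** Such a variable may lie on the hypothesised pathway and can still predict POSD. Arm is needed for a claim of independence or mechanism, not for prediction as such.

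**Conclusion.** The concern holds for the step 3 intervals. Followed as written on one set of patients, the procedure reports intervals labelled 95% whose coverage among selected variables was about 30% to 80% in every null scenario tried. At least one false significant predictor appeared in about 8% to 70% of trials. The size depends on the assumed EEG correlations and the unstated penalty rule; the direction does not.

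The point about arm is separate and conditional. Unless arm is in the model, an EEG variable shifted by 0.5 to 0.8 SD (an assumption; the documents give no figure) is more likely to be named a predictor through arm alone: 23% to 33% for the four shifted variables together, against about 11% with arm included.

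Severity is limited. The analysis is exploratory, and the primary chi-square test and its risk difference are unaffected. It should still be changed before the data are analysed.

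**What to change.** In section 2.11 or the analysis plan:
- Drop the univariate screen.
- Run LASSO on all 30 EEG variables with treatment arm forced in unpenalised. Forcing in baseline AIS as well is optional.
- Repeat the whole selection, including the penalty choice, in bootstrap samples. Report selection frequencies, penalised coefficients and an optimism-corrected AUC.
- Remove the step 3 odds ratios and intervals, or label them exploratory and not valid for inference after selection.
- Do not describe the selected variables as independent predictors.

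This costs analysis code only. It needs no new data or participants and does not touch the primary analysis. The downside is less striking exploratory results.

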## Discussion

3

This study investigates the clinical efficacy and underlying mechanisms of taVNS in alleviating POSD after gynecologic laparoscopic surgery by modulating brain rhythm stabilization, employing a randomized controlled trial design. POSD frequently occurs after gynecologic surgery, heightening the risk of postoperative pain, cognitive dysfunction, and cardiovascular events, thereby extending recovery time. Current treatments like benzodiazepines and melatonin focus on symptomatic relief without addressing the neurophysiological regulation of the sleep-wake cycle, and they offer limited effectiveness in managing complex, multi-dimensional issues synergistically. Cortical rhythmic activity serves as the core neurophysiological mechanism regulating the sleep-wake cycle; surgical stress and anesthetic agents can disrupt the power balance of cortical slow waves and fast waves, leading to fragmented sleep architecture. This study explores the innovative use of taVNS, a non-invasive neuromodulation technique, for postoperative sleep management by leveraging the central role of cortical oscillations in sleep homeostasis, aiming to offer a novel multi-target therapeutic strategy.

The association between EEG characteristics and POSD establishes a physiologically targetable endpoint for perioperative neuromonitoring. In a prospective cohort study, Dai et al. (26) demonstrated that reduced sleep spindle density in frontotemporal channels during surgery independently predicted POSD in elderly patients undergoing orthopedic procedures, confirming that specific EEG oscillatory patterns serve as predictive biomarkers for postoperative sleep disruption. Prior work establishes that intraoperative EEG signatures are modifiable targets rather than mere predictors of postoperative sleep quality. In gynecologic laparoscopy specifically, enhancing frontocortical beta and gamma power through esketamine administration reduces POD 1 sleep disturbance incidence (1). Similarly, elevated intraoperative gamma-band activity correlates with sleep protection in breast cancer surgery, suggesting a cross-surgical class effect (27). These convergent findings indicate that perioperative cortical oscillatory states are therapeutically accessible, providing the mechanistic premise for non-pharmacologic neuromodulation.

Accumulating evidence indicates that taVNS exerts therapeutic effects through modulation of cortical oscillatory activity (28, 29). An animal study found that taVNS can significantly improve the power spectrum of the delta band, reduce the power spectrum of the β band in EEG signals of insomnia model rats (30), and inhibit the excited state of the cerebral cortex in insomnia model rats. Furthermore, EEG reveals that taVNS normalizes alpha-band activity in the prefrontal cortex of patients with chronic pain, indicating reduced cortical hyperarousal (31). Randomized sham-controlled trials indicate that taVNS significantly improves sleep quality scores (Cohen’s *d* = 1.2), enhances slow-wave sleep continuity, and boosts daytime functioning in patients with chronic insomnia (32). Studies have found that taVNS can increase frontal delta power and right-lateralized delta asymmetry during resting states, suggesting enhanced homeostatic sleep pressure (18). However, its use for acute POSD after gynecologic surgery remains unexplored.

In this study, subjective sleep quality was evaluated utilizing the Athens Insomnia Scale (AIS), a rigorously validated instrument characterized by strong psychometric properties, which has been widely employed in numerous investigations examining postoperative sleep quality (33–35). Nevertheless, subjective scales are susceptible to recall bias and provide no information on sleep architecture; therefore, objective sleep parameters will be acquired concurrently. Given the practical constraints of conducting standard polysomnography (PSG) during the perioperative period, we will employ the HUAWEI WATCH GT2 smartwatch for objective sleep monitoring (validated against PSG: sensitivity 95.9%, accuracy 87.3%) (36) to obtain continuous physiological parameters, including sleep efficiency and wake after sleep onset. Moreover, taVNS’s influence on autonomic tone and possible decrease in perioperative anxiety (measured by the HADS-A subscale) might indirectly enhance sleep quality, thus breaking the cycle of sleep disturbances, increased pain, and prolonged recovery. Multidimensional scales such as the QoR-15 and NRS effectively indicate clinical symptom improvement and intervention efficacy in postoperative patients.

In addition, preoperative intervention can enhance the tolerance of the central nervous system to anesthetic interference (37), while the early post-anesthesia emergence period represents a critical window for rhythm reshaping (12); therefore, a dual-timepoint strategy combining preoperative and immediate postoperative interventions may be more effective. The non-invasive and easy-to-administer nature of taVNS renders this dual-timepoint approach clinically feasible.

This study makes three significant contributions. Theoretically, it integrates taVNS with perioperative neuroplasticity theory to enhance postoperative sleep management. By focusing on cortical rhythmic activity as the central mechanism, this approach transcends pharmacological methods that merely offer symptomatic relief without restoring neurophysiological homeostasis, thereby transitioning from passive sedation to active state reconstruction. Methodologically, the study employs a randomized, double-blind, sham-controlled design. The sham protocol involves titrating the current to the threshold of tingling sensation, followed by immediate cessation, while keeping the device powered to ensure blinding. For assessment, a comprehensive three-dimensional evaluation framework is constructed, incorporating subjective sleep outcomes, objective sleep parameters, and mechanistic measures. This framework facilitates correlation analysis between cortical oscillatory dynamics and sleep outcomes.

From a methodological perspective, the intervention protocol employed in this study is designed to adhere to standard taVNS parameters. The stimulation will be administered to the left cymba conchae, a region abundant in auricular vagal branches, at a frequency of 20 Hz with a pulse width of 250 μs. These parameters were selected based on previous efficacy studies related to chronic insomnia and cortical oscillation research, aiming to optimize the balance between tolerability and effective activation of the vagus nerve-thalamus-cortex pathway (32, 38). The sample size calculation is informed by internal pilot data, indicated a reduction in the incidence of POSD, defined as AIS score of 6 or higher, from 45% in the sham group to 20% in the taVNS group–an absolute risk reduction of 25 percentage points. To achieve 80% statistical power for detecting this difference in proportions at a two-sided significance level of α = 0.05, while accounting for a 10% dropout rate, a sample size of 58 participants per group will be required.

This study is subject to several limitations. To begin with, the single center design might restrict how widely the findings can be applied, since local patient traits like age distribution, initial sleep condition, and the complexity of surgeries could influence the intervention’s effectiveness. Nevertheless, the single-center setting enables standardization of surgeons, anesthesia protocols, and postoperative ward environments, thereby reducing confounding from institutional practice variations that frequently obscure treatment effects in multicenter perioperative trials. Secondly, our sample size estimation relies on internal pilot data. With a total of 116 participants, the study lacks sufficient power for conducting subgroup analyses, detecting rare adverse events, or making stratified comparisons based on age, operative duration, or anesthetic dosage. Thirdly, the primary observation window of 3 days may not capture longer-term effects on chronic sleep disturbances, delayed cognitive function, or sustained autonomic regulation.

Even with these limitations, the potential significance of this study is remarkable. Should taVNS be effective, it may offer a safe and economical non-drug approach to managing sleep disturbances after gynecologic surgery, fitting well within the multi-faceted symptom management of ERAS protocols. Even if null, the mechanistic EEG data and careful sham-controlled design would inform parameter selection, biomarker reliability, and the feasibility of perioperative neuromodulation trials. This research could uncover how cortical oscillatory activity regulates POSD, offer new insights into the role of the vagus nerve-thalamus-cortex pathway in perioperative care, and enhance comprehension of interactions between neural, autonomic, and sleep systems.
